### Intervention: the preemie-test

The preemie-test assessment occurs as soon as possible after birth, in the first 24 hours, inside incubators, open heating crib, common crib or in the mother’s lap, in order to ensure minimum manipulation and stable clinical conditions. The acquisitions of all newborns will be stored in a database for further statistical analysis.

A non-invasive, handheld optoelectronic prototype has been developed to measure the backscattered light signal from the skin.^15^ The equipment regulates the emitted light and processes the received light signal in the sensor, resulting in the prediction of GA by a mathematical model, associated or not with clinical variables. According to the Brazilian regulatory health agency (ANVISA), this medical device is categorised as a Class II safety: non-invasive and medium risk. The prototype unit of measurement and the process of GA estimation were patented under number BR1020170235688 (CTIT-PN862).^14^ An updated version of the invention received improvements in order to safeguard reliability and to minimise examiner interferences on the skin’s backscattering acquisition. The light emitting-sensor touches the skin over the sole of the foot for a few seconds. The skin reflectance will be sensed once the light has been emitted by a light emitting diode at wavelengths from 400 nm to 1200 nm. Data acquisitions occur automatically, without operator influence and are obtained three times per newborn, in the same site and sequentially. Digital recordings will be uploaded to a server for further analysis. The prototype will blind the examiner to the predicted GA value.

The criterium for discontinuing the interventions for a given trial participant will be in case of parents of the newborns' request.

### Training and monitoring

Systematic monitoring of data collection, through an electronic information system, would trigger any adverse event. This medical team is still responsible for the training of healthcare professionals to recruit participants, data collection, a safely performed preemie-test during the newborn’s assessment and the monitoring of data quality. The certification of co-participant centres involved the accomplishment of at least 30 simulated examinations by the participant health professionals in the study.

### Gestational age methods of calculation and comparators

Reference-GA (R) is calculated on enrolment, using the embryo measurement assessed by ultrasound exam at <14 weeks of gestation as a reference. Crown-rump-length (CRL) data, recorded from the ultrasound report or prenatal care book-document, will be considered the crude data, when available. Intergrowth’s 21st standard curve for ultrasound measurements from 7 weeks and 3 days up to 13 weeks and 6 days will be adjusted to all GA data, according to CRL.^18^

GA methods to calculate GA in the childbirth setting, and their comparators are as follows:Preemie-test-GA (T): data statistically determined by analysing the acquired information stored in the device’s processor.Comparators-GA (C): calculated using the first ultrasound exam after 13 weeks and 6 days of gestation and before 22 weeks (C1). When available, a second comparator is GA based on a reliable LMP (C2).^13^

We will take a scanning copy of the prenatal care book or the ultrasound report. After evaluating the data quality, the images will be discarded. To achieve a reliable LMP, we will interview the woman, as suggested by Nguyen *et al*.^13^

### Primary outcome measures

The primary target is the agreement between the GA offered by the preemie-test (T) and the GA calculated by the comparators (C1 and C2), so as to perform the new test in scenarios without the Reference-GA (R). The outcome is the difference between the GA calculated by the photobiological neonatal skin assessment methodology in relation to the age calculated by the comparators.

Another measure for the primary target is the detection of preterm newborns, considering the age before 37 weeks of pregnancy as the threshold between term and preterm births, and analysing sub-categories of preterm birth, based on GA^4^:Extremely preterm (<28 weeks).Very preterm (28–32 weeks).Moderate to late preterm (more than 32 to <37 weeks).

In this case, the outcome is the proportion of the preterm newborn correctly detected at birth, based on the photobiological test of the skin, within a 1-week error.

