**Trial registration number:**

RBR-3f5bm5.

Strengths and limitations of this study:Prospective multicenter evaluation of a new medical device with training, and certification of collaborative centres.The gold standard comparator for pregnancy dating does not exist; instead a reference standard will be used with blinded primary outcome.The agreement endpoint between methods for gestational age determination precludes randomisation of the intervention.

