Current methods of dating pregnancy remain a worldwide challenge. Early obstetric ultrasound currently offers the best due date.^7^ However, access to this type of exam is limited because of high equipment costs, poor training and skills of health professionals, or late prenatal care.^8^ Despite a 10-days or more margin of error during the second and third trimester of gestation, ultrasound is still a reasonable methodology for GA determination, when the best opportunity was lost.^7^ The calculation, based on the historical information of the last menstrual period (LMP), is impacted by the uncertainty of both the fertility days and date of conception,^9^ due to the bias of memory, the use of hormonal contraception and breastfeeding.^10^ After birth, neurological scores, such as the New Ballard,^11^ show a tendency to overestimate GA in preterm infants and underestimate GA in growth-restricted infants.^12^ Efforts to enhance the reliability of pregnancy dating, through more accurate and accessible technologies, seek to improve pregnancy outcomes and neonatal survival.^13^

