### Eligibility criteria and participant’s timeline

A prospective sequential and concurrent enrollment process will select newborns in referral hospitals centres for neonatal care. Infants are eligible with the following inclusion criteria: (1) alive newborn; (2) enrollment during first 24 hours of life; (3) be 24 weeks or more of GA, at birth; (4) fetus underwent an obstetric ultrasound assessment before 14 weeks of pregnancy and (5) fetus also had obstetric ultrasound assessment between 14 and 22 gestational weeks. Exclusion criteria are: (1) malformation with structural skin alterations and (2) skin modifiers: anhydramnios, hydrops, congenital skin diseases or chorioamnionitis. Randomisation was not appropriate to assess the agreement between different methods to assess pregnancy dating.

In a nested case–control study, we will select newborns within the first 72 hours of life, discharge or death, whichever occurs first, with the following inclusion criteria: (1) RDS or (2) tachypnoea of the newborn (TTN) diagnosis. Ranges of GA will randomly pair controls. Exclusion criteria include: (1) the existence of extra pulmonary conditions with tachypnoea not due to prematurity and (2) diagnosis of Clinical or Laboratory-Confirmed Bloodstream Infection.

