### Secondary outcome measures

In a simulated scenario, in which the Reference-GA (R) is unknown, two groups will be randomly assigned from the complete database in order to compare differences among the Reference-GA (R), the GA obtained through the preemie-test (T) and the GA calculated by the comparators. Figure 1 presents such subgroups and measures for comparison.To monitor the device’s safety when in regular use by participants over a 72-hours period. Adverse events will be monitored, according to ISO 14155:2011 standards. This means any unexpected medical events, unintended disease or injury or unfortunate clinical signs in subjects, users or other people, whether related to the investigational medical device or not.To establish the *ease of use* of the preemie-test measurement as a potential method for preterm newborn diagnosis.

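### The primary agreement outcome sets the test against second-trimester ultrasound and LMP and leaves the better Reference-GA to a secondary simulation, so device error cannot be separated from comparator error

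*Protocol article*

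**What the plan says.** All references are to the protocol article.

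- **Primary outcome measures** puts the main aim in these words: "The primary target is the agreement between the GA offered by the preemie-test (T) and the GA calculated by the comparators (C1 and C2". The reason given is "so as to perform the new test in scenarios without the Reference-GA (R". The outcome itself is the difference between test and comparator GA. The Abstract describes it the same way.
- **Eligibility criteria:** criterion 4 is that the "fetus underwent an obstetric ultrasound assessment before 14 weeks of pregnancy", and criterion 5 that the "fetus also had obstetric ultrasound assessment between 14 and 22 gestational weeks".
- **Gestational age methods of calculation and comparators:** R is obtained "using the embryo measurement assessed by ultrasound exam at <14 weeks of gestation as a reference". C1 comes from the first scan after 13 weeks 6 days and before 22 weeks. C2 is used only when a reliable LMP is available.
- **Introduction:** early ultrasound is ranked as giving the best due date. Later ultrasound is called reasonable "Despite a 10-days or more margin of error during the second and third trimester of gestation". LMP dating is described as uncertain, without a figure.
- **Secondary outcome measures:** R appears in a simulated scenario where "two groups will be randomly assigned from the complete database in order to compare differences among the Reference-GA (R"), T and the comparators. Details are left to Figure 1, which is not shown.
- **Data analysis:** the primary agreement among three unnamed methods is assessed by ICC, Bland-Altman plots and paired t-tests. The database is split at random into a training and a validation subsample.

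**The concern.** The study sets out to validate a device for estimating gestational age. Every eligible infant has the scan that yields R, which is the dating the article itself ranks highest. The main agreement measure is nevertheless taken against the two methods it ranks lower.

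The intended use in settings without R explains where the device will be used. It does not explain why R should be set aside while the device is being validated and R is at hand. The question for those settings is whether T comes as close to the best dating as C1 or C2 does. T-C does not answer it: if T and C1 disagree, either could be at fault, and if they agree, they may share an error. At stake is whether the headline result can be read as a property of the device.

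**Working it through.** **1. The plan's own figure.** Sampling and sample size gives 787 for a paired t-test with a 10% effect size, alpha 0.05 and power 0.80. Read the effect size as dz = mean difference / SD of differences = 0.10, two-sided.

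- Normal approximation: n = (1.960 + 0.842)² / 0.10² ≈ 785.
- Noncentral t: n = 787, power 0.8001. The figure reproduces. One-sided alpha would give 620.

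Because dz is standardised, 787 does not depend on which GA is subtracted from T, so replacing C by R leaves it unchanged.

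**2. Which dating exists in which infant**

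| GA | Source | In every infant? | Article's own view |
|---|---|---|---|
| R | scan before 14 weeks | scan required (criterion 4) | best dating |
| C1 | scan at 14 to 22 weeks | scan required (criterion 5) | margin of 10 days or more |
| C2 | reliable LMP | only when available | uncertain, no figure |

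T, R and C1 can therefore be compared within the same infant.

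**3. What T-C contains.** Let e be each method's error around true age, with SDs σT, σC, σR. Then T-C = eT - eC and

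Var(T-C) = σT² + σC² - 2ρσTσC, where ρ is the correlation of eT and eC.

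The data give one variance for two unknown SDs and an unknown correlation, so the device's part cannot be extracted. The mean of T-C is bias(T) - bias(C), so random comparator error leaves it unchanged and only a biased comparator shifts it. What random error affects is the limits of agreement and the ICC.

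**4. Illustration.** Assumptions, none fixed by the document: independent errors (ρ = 0); 10 days read as a 95% half-width, so σC = 10/1.96 ≈ 5.1 days; σT = 7 days; σR from 0 to 3 days.

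- Against C1: SD = √(49 + 26.0) = 8.66; limits ±1.96 × 8.66 = ±17.0 days.
- Against R, σR = 0: ±1.96 × 7 = ±13.7 days.
- Against R, σR = 3: SD = √(49 + 9) = 7.62; limits ±14.9 days.

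**5. Range over the assumptions** (half-width of the 95% limits, days, ρ = 0)

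| Device SD | vs C1, SD 5.1 | vs C1, SD 10 | vs R, SD 0 to 3 |
|---|---|---|---|
| 5 | 14.0 | 21.9 | 9.8 to 11.4 |
| 7 | 17.0 | 23.9 | 13.7 to 14.9 |
| 10 | 22.0 | 27.7 | 19.6 to 20.5 |
| 14 | 29.2 | 33.7 | 27.4 to 28.1 |

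The widening is 4% to 43% if 10 days is a 95% margin and 20% to 124% if it is an SD.

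**6. Correlated errors.** With σT = 7 and σC = 5.1, Var(T-C) falls below σT² once ρ exceeds σC/(2σT) = 5.1/14 ≈ 0.36. At ρ = 0.5 the variance is 49 + 26.0 - 35.7 = 39.3, the SD is 6.3 and the limits are ±12.3 days, narrower than the device's own ±13.7. Agreement would then look too good.

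**7. What R adds.** If R's error is independent of the other two, Var(T-R) - Var(C1-R) = σT² - σC². R's own error cancels, so R need not be perfect to show which of T and C1 is closer to true age.

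**The case against.** The strongest reply is that agreement with the method in actual use is a legitimate method-comparison question, and the article gives its reason for asking it. Where no early scan exists, C1 or C2 is what a clinician would have. R is also imperfect: the article says that no gold standard exists, and CRL is used only when available. This justifies reporting T-C1 and T-C2. It does not make them the better primary measure when R is available for the same infants.

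Several stronger readings are tempting but not supported:

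- *That R is ignored.* It is used in the first-listed secondary outcome. The issue is its rank.
- *That the device will look worse than it is.* This needs independent errors. The target on which the model is trained is not stated, and shared dependence on fetal size is possible, so the direction could reverse (step 6).
- *That T-C is judged against a 1-week margin tighter than the comparator's error.* The 1-week tolerance belongs to preterm detection, not to the T-C difference.
- *That the two random groups waste precision.* The text does not say which difference is taken in which group, and Figure 1 is not shown.
- *That the strengths list contradicts the outcome.* Its statement that "instead a reference standard will be used with blinded primary outcome" may use the generic diagnostic term rather than mean R. The wording is unclear rather than clearly contradictory.

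**Conclusion.** The point holds as a matter of rank. The primary difference is taken against C1 and C2 and R is kept for a secondary simulation, although the scans for R and C1 are required in every infant and the article ranks early ultrasound best. T-C alone cannot attribute poor agreement to the device, and it cannot show whether T is as good as C1 or C2 where R is missing. This follows from the outcome definition and needs no numerical assumption.

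The size does need assumptions. The article gives no device SD and does not say whether 10 days is an SD or a 95% margin. Its figure also pools the second and third trimesters, so it is not specific to C1. Under step 4 the limits are ±17.0 days against C1 and ±13.7 to ±14.9 against R. Other plausible inputs move the widening between 4% and 124%, and correlated errors could reverse it. This is a worthwhile and cheap improvement. It does not show that the planned results would be wrong in a known direction.

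**What to change.** 1. Make T-R the primary agreement outcome, with T predicted out of sample: either in the validation subsample of Data analysis or by cross-validation.
2. Name R as the standard that defines preterm status.
3. Compare |T-R| with |C1-R| within the same infants, and with |C2-R| where a reliable LMP exists.
4. Keep T-C1 and T-C2 as secondary agreement measures.
5. Align the wording of the Abstract, the strengths list, Primary outcome measures, Secondary outcome measures and Data analysis, and name the three methods.

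**Cost.** No new data are needed and the 787 calculation is unchanged. If only the validation subsample is used, the analysed number is smaller than 787, but that applies equally to an out-of-sample T-C. The change of the registered primary outcome must be recorded, with its reason, before analysis. R's quality will vary because CRL is not always available, so report how R was obtained and repeat T-R in infants with recorded CRL. R and C1 are both ultrasound-based, and any shared error would favour C1 in the benchmark. That should be stated when the comparison is reported.

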## Abstract

**Introduction:**

Recognising prematurity is critical in order to attend to immediate needs in childbirth settings, guiding the extent of medical care provided for newborns. A new medical device has been developed to carry out the preemie-test, an innovative approach to estimate gestational age (GA), based on the photobiological properties of the newborn’s skin. First, this study will validate the preemie-test for GA estimation at birth and its accuracy to detect prematurity. Second, the study intends to associate the infant’s skin reflectance with lung maturity, as well as evaluate safety, precision and usability of a new medical device to offer a suitable product for health professionals during childbirth and in neonatal care settings.

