### Data analysis

Demographics and baseline characteristics of the study group, as well the intervention measurements, will be summarised by the frequencies and the mean and standard deviation (SD), whereas the median and interquartile range (IQR) will be preferred for non-normally distributed continuous variables.

To model the GA prediction, computational randomisation will select two subsamples in the database. One of them to train the prediction model of GA based on skin reflectance and clinical variables, such as sex, time in an incubator, phototherapy, birth weight, among others. Another part will be for the analytical validation of the predictive model. Improvements in the existing prediction models for GA (preemie-test), will be conducted with conventional statistical and data mining analyses.

Regarding the primary endpoint, the agreement among three methods for GA will be calculated using the Intraclass coefficient correlation and Bland & Altman plots,^23^ and paired t-testing. The accuracy of the preemie-test in identifying the premature newborn, within a 1-week margin of error, will be the target of the accuracy analysis.

The relationship between the measurement of the newborn’s skin reflectance and complications due to pulmonary distress associated with immaturity will be evaluated by means of association tests and risk. The significance level for hypothesis tests will be 5%, together with 95% CIs.

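### The preterm-detection measure is a sensitivity only, so false positives among term infants never enter it, and its 1-week tolerance has no single meaning

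*Protocol article*

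**What the plan says.** The abstract gives the aim: "this study will validate the preemie-test for GA estimation at birth and its accuracy to detect prematurity".

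Primary outcome measures then sets two measures for the primary target. The first is agreement: "The outcome is the difference between the GA calculated by the photobiological neonatal skin assessment methodology in relation to the age calculated by the comparators". The second is introduced with "Another measure for the primary target is the detection of preterm newborns", and the article draws the line between term and preterm at 37 weeks. Its definition for this second measure reads: "the outcome is the proportion of the preterm newborn correctly detected at birth, based on the photobiological test of the skin, within a 1-week error".

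The Data analysis section returns to it once: "The accuracy of the preemie-test in identifying the premature newborn, within a 1-week margin of error, will be the target of the accuracy analysis". The same section splits the database at random into a part that trains the prediction model and a part that validates it.

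Sampling and sample size plans 392 term infants, 263 infants of 32 to 36 completed weeks and 132 of 24 to 31 completed weeks.

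**The concern.** There are two separate faults.

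- **One-sided denominator.** A proportion taken among preterm infants is a sensitivity. Accuracy at a term/preterm threshold also needs the proportion of term infants correctly left unflagged. About half the planned sample is term, and none of those infants can change this outcome. Any move that makes the device call more infants preterm can raise detection, and its cost in false positives stays out of the measure.
- **Undefined tolerance.** The 1-week allowance might relax the 37-week cut-off, forgive near misses, or require the estimated age to lie within a week of the true age. The first two loosen the measure and the third tightens it sharply. The Data analysis section repeats the margin without explaining it.

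At stake is whether this measure of the primary target can support a claim about detecting prematurity, and whether its value is fixed before the data are seen.

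**Working it through.** **1. The plan's own figure.** A paired t-test with standardised difference 0.10, two-sided alpha 0.05 and power 0.80 gives n = 787 by the noncentral t (power 0.8001). The normal approximation is ((1.960 + 0.842)/0.10)² ≈ 785. So 787 reproduces, but for the agreement measure. No target or sample size is given for detection.

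**2. Who enters the detection measure.** Preterm: 263 + 132 = 395, and 395/787 = 50.2%. Term: 392/787 = 49.8%, outside the measure.

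**3. A device that labels every infant preterm.**
- If the tolerance loosens the preterm label or does not constrain it: score 395/395 = 100%, specificity 0/392 = 0%, overall accuracy 395/787 = 50.2%.
- If the estimate must also lie within 1 week of true age: the 100% no longer follows. Take a device that returns one constant age, say 36 weeks, with ages uniform within each preterm band. It is right only for true ages 35 to 37, that is (263 × 2/5)/395 = 26.6%, and no constant below 37 weeks does better.

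**4. How far the readings differ on the same data.** The assumptions are mine, except R² = 0.828, which the article's Introduction reports for the feasibility model:
- Ages are uniform within the three planned bands, with the term band ending at 41 or 42 weeks.
- Mean age for the 41-week limit is (392 × 39 + 263 × 34.5 + 132 × 28)/787 = 35.65.
- The variance is the weighted sum of band width²/12 and squared distance from that mean: (392 × 12.55 + 263 × 3.41 + 132 × 63.87)/787 = 18.10, so SD = 4.25. For the 42-week limit the SD is 4.50.
- Error model U (unbiased): T = GA + e, SD(e) = SD × √(1 − 0.828), giving 1.76 or 1.86 weeks.
- Error model S (regression predictor, shrunk to the mean): T = mean + 0.828 × (GA − mean) + e, SD(e) = SD × √(0.828 × 0.172), giving 1.61 or 1.70 weeks.
- Errors are normal. Each proportion is Φ((cut-off − E[T])/SD(e)) averaged over the bands.

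| Term limit, model | T<37w, preterm | T<38w, preterm | Error ≤1 week, preterm | Specificity at 37w | Specificity at 38w |
|---|---|---|---|---|---|
| 41, S | 91.5% | 96.7% | 42.0% | 77.5% | 58.9% |
| 41, U | 90.6% | 95.8% | 42.9% | 82.6% | 68.0% |
| 42, S | 90.6% | 96.1% | 40.1% | 81.4% | 66.1% |
| 42, U | 90.1% | 95.4% | 40.8% | 85.2% | 73.3% |

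Relaxing the cut-off by a week adds about 5 points to the measure and removes 12 to 19 points of specificity. The outcome as written would show only the gain.

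**5. A cruder check.** With unbiased normal errors of SD 1, 1.5 and 2 weeks and term ages uniform over 37 to 41, moving the cut-off from 37 to 38 weeks raises sensitivity from 94.7 / 92.0 / 89.4% to 98.9 / 97.0 / 94.7%. The term false-positive rate rises from 10.0 / 14.9 / 19.5% to 27.1 / 30.4 / 33.4%. The direction is the same.

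**6. Does the agreement measure fill the gap?** In models U and S the mean of T minus true age is zero over the whole sample, yet 15 to 23% of term infants fall below 37 weeks. A mean difference near zero therefore does not give the false-positive rate at the threshold.

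**The case against.** Four points can fairly be made against this.

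- **The always-preterm device.** A reader might infer that such a device necessarily scores 100%. The article does not support that without a condition. If the tolerance demands an estimate within a week of true age, over-calling earns nothing and shifting all estimates down can lower the score. This stands. On that reading, though, the measure is age agreement among preterm infants rather than detection, and it still omits term infants.
- **False positives in the study as a whole.** A reader might infer that they are ignored altogether. The article does not show that. An accuracy analysis is planned, term infants are enrolled, and the choice of further indices may sit in a fuller document. This stands as a limit on the claim. It does not rescue the outcome: the article states a definition, that definition is one-sided, and the accuracy analysis names the same target with the same margin.
- **The agreement measure.** It is not restricted to preterm infants, so a device shifted down far enough to flag everyone would show a large negative bias. This stands for gross under-dating. It does not supply a false-positive rate at 37 weeks.
- **The figures.** R² comes from a feasibility model that the article plans to improve, so the percentages are illustrative. This stands, and it is why ranges are given.

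**Conclusion.** The concern holds in a limited form. The detection measure covers 395 of 787 planned infants and cannot register a false positive among the other 392, which does not match an aim of accuracy in detecting prematurity. That loss comes from the preterm-only denominator, not from the tolerance.

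The tolerance is a separate fault: one data set could yield roughly 40–43%, 90–91% or 95–97% depending on how it is read, with an unreported specificity of about 77–85% at 37 weeks or 59–73% at 38. These sizes rest on R² = 0.828, normal errors, uniform ages within bands and a term limit of 41 or 42 weeks. The one-sided denominator and the ambiguity rest on the wording alone.

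The 100% score for a device that calls everyone preterm is conditional on a loosening or non-binding tolerance. It should also not be inferred that all 392 term infants can supply the specificity: those used to train the model would flatter it.

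**What to change.** - Define the detection outcome as sensitivity and specificity of T below 37w0d against Reference-GA below 37w0d, each with a 95% CI and with no tolerance at the threshold.
- Estimate both in the validation subsample described under Data analysis, using its preterm and term infants.
- Report the share of infants with |T − R| of at most 7 days as a separate agreement measure, which is where a 1-week margin belongs.
- Use the same definition in Primary outcome measures and Data analysis. A ROC area is optional.

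**Cost.** This is a wording change, with no new data and no change to N = 787. The reported detection rate would be about 5 points lower than under a cut-off relaxed by a week. Specificity would rest on the validation share of term infants only. The article gives no split. If half were used (196) and specificity were 80%, the 95% half-width would be 1.96 × √(0.80 × 0.20/196) = 5.6 points, against 4.0 points if all 392 could be used.
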